### Statistical analyses

To compare and confirm cognitive deficits, including PM, between HF patients and a healthy matched control, group differences in baseline PM and neuropsychological tests will be examined using inferential statistics (*t*-test and analysis of variance; ANOVA). To analyse the changes in each measure assessed at each time point (baseline, Assessment One and Assessment Two) we will use separate mixed ANOVAs for all dependent variables. The within-groups variable will be *testing phase* (baseline, Assessment One, Assessment Two) and the between-groups variable will be *Training group* (PM training, word puzzles). Multiple regression analysis will be performed to identify whether physical, cognitive, emotional and mental functioning variables are independent predictors of HF self-care and consulting behaviours, after adjusting for clinical characteristics. For all analyses, α levels will be set at 0.05 and effects sizes will refer to partial η-square values.

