**Table 1 Tab1:** **Assessment measures at baseline and post-intervention evaluations**

**Measures**	**Baseline**		
		**Assessment One** ^**b**^	**Assessment Two** ^**c**^
Physical functioning			
Physical examination (BP/HR/RR/weight/NYHA class, BNP)	X	X	X
Echocardiogram	X		X
‘Up and Go’ test	X	X	X
Timed Instrumental Activities of Daily Living (TIADL)	X	X	X
Unplanned readmission/survival		X	X
Self-care			
Heart-FaST	X		X
Patient engagement in self-care: (SCHFI and four consulting items from the EHFScBS)	X	X	X
Nurses and carer assessment of patient engagement in self-care	X	X	X
Review of patient symptom monitoring diary and how they perform self-care maintenance behaviours		X	X
Control Attitudes Scale - Revised (CAS-R)	X	X	X
Psychosocial functioning			
Quality of life (SF-12)^a^	X	X	X
Dyadic HF care typology	X		
Hospital Anxiety and Depression Scale (HADS)^a^	X	X	X
Cognitive functioning for HF patients			
Cognitive screen (MoCA)^a^	X	X	X
Assessment of PM (MIST, brief version of Virtual Week and naturalistic task)^a^	X	X	X
Working memory, executive functioning, verbal memory (CogState, N-Back, Trail Making Test)^a^	X	X	X
Premorbid intelligence (NART)^a^	X		
Caregiver			
Health screening questionnaire	X		
Caregiver (or next of kin) Contribution to Self-Care (CC-SCHFI)	X	X	X
Control Attitudes Scale - Revised (CAS-R)	X	X	X
Dyadic HF care typology	X		
Quality of life (SF-12)^a^	X	X	X
Modified Caregiver Strain Index (MCSI)	X	X	X
Proxy - IADL	X	X	X

Key: BNP, brain natriuretic peptide; BP, blood pressure; CC-SCHFI, Caregiver Contribution Self-Care Heart Failure Index; EHFScBS, European Heart Failure Self-care Behaviour Scale; Heart-FaST, Heart Failure Self-care Screening Tool; HF, heart failure; HR, heart rate; IADL, Instrumental Activities of Daily Living; MIST, Memory for Intentions Screening Test; MoCA, Montreal Cognitive Assessment; NYHA class, NART; National Adult Reading TestNew York Heart Association Classification; PM, prospective memory; RR, respiratory rate; SCHFI, Self-Care Heart Failure Index; SF-12, Short-Form 12-item health survey.

^a^Measures will also be collected from healthy non-HF controls at baseline; ^b^2 to 4 weeks post cognitive training; ^c^12 months post cognitive training.

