### Sample size

Based on data from other relevant trials of patient education and HF self-care, an eight-point difference in standardised self-care scores is a clinically important change [73]. Using the G*power calculator it was estimated that in order to achieve an 80% power at a 0.05 significance, a sample size of 63 per group is required to detect a small to medium effect of the self-care intervention on hospitalisations [73]. Using analysis of covariance (ANCOVA) to examine for clinically significant differences in standardised self-care maintenance and management scores between the 2 HF groups, a total of 100 patients in each group (200 in total) will have > 90% power (α of 0.05) to detect a medium effect size (f^2^ = 0.4) in the primary endpoint. The probable requirement to undertake non-parametric statistical analyses (due to non-Gaussian distributed data) has been factored into study power calculations in addition to a 20% intervention refusal rate and loss to follow-up. The sample size for the comparison of baseline cognitive performance (in particular PM) between 60 HF patients and a healthy age-matched control group has been based on previous studies [55,74]. As such, the sample size has the power to detect significant differences with moderate effect sizes.

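### The primary endpoint is powered on ANCOVA, but the analysis section plans a three-phase mixed ANOVA without baseline adjustment and does not say which term tests treatment

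*Protocol article*

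**What the plan says.** The Sample size section describes the primary comparison as "Using analysis of covariance (ANCOVA) to examine for clinically significant differences in standardised self-care maintenance and management scores" between the two heart failure groups. It states that 100 patients per group "will have > 90% power (α of 0.05) to detect a medium effect size", printed as f² = 0.4. It calls eight points on the standardised self-care score clinically important, and says that 20% refusal and loss to follow-up has been allowed for.

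The Statistical analyses section does not mention ANCOVA. Its sentence on change over time opens with measures assessed at baseline, Assessment One and Assessment Two, and continues: "we will use separate mixed ANOVAs for all dependent variables". Testing phase (three levels, baseline included) is the within-patient factor and training group the between-patient factor. The section adds "For all analyses, α levels will be set at 0.05" and "effects sizes will refer to partial η-square values".

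The Outcomes section makes the primary outcome self-reported self-care (SCHFI) together with carer, researcher and nurse assessments. In Table 1 the researcher's item, "Review of patient symptom monitoring diary and how they perform self-care maintenance behaviours", is collected at Assessments One and Two only, as is readmission/survival. The description of the SCHFI says that its management score exists only for patients with ankle swelling or breathing trouble in the preceding three months.

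**The concern.** An ANCOVA and a 3 × 2 mixed ANOVA are different analyses of a randomised comparison, and the article gives one for sizing and the other for testing. Four consequences follow.

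- Baseline is measured before randomisation, so its expected group difference is zero. The mixed ANOVA nevertheless makes it one of three outcome levels. The group main effect is then averaged over a phase where no effect can exist.
- The group-by-phase interaction has two degrees of freedom. It tests whether the arms' profiles differ anywhere, and it is not an effect at a stated time. The text does not say whether this term or the main effect is the treatment test.
- In its classical form the method uses only patients with all three assessments. A patient who dies or is lost before 12 months would then also lose the Assessment One data. For SCHFI management, only patients with recent symptoms at every visit would remain.
- The diary and self-care review (part of the primary outcome) and readmission/survival lack the baseline level that the three-phase model needs, and the second is an event outcome.

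At stake are efficiency, the set of patients analysed, and whether the result can be read against eight points.

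**Working it through.** **Inputs.** From the article: two-sided α 0.05 (sidedness is not stated and is assumed), 100 per arm, 1:1 allocation, 20% refusal and loss (so 80 completers per arm), and an effect size of 0.4. Not given, hence assumed: the correlation ρ between assessments (0.3, 0.5 and 0.7, compound symmetry) and the standard deviation of the score.

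**The article's own figures.** For two equal groups d = 2f. Printed f² = 0.4 gives f = 0.632 and d = 1.26; if f = 0.4 was meant, d = 0.80. With 100 per arm and no credit for the covariate, power is about 100% at d = 1.26, 99.99% at d = 0.80 and 94.0% at d = 0.5. The claim of more than 90% is true under each reading. The section's other figure, 63 per group at 80% power, is recovered with d = 0.5: 2 × (1.96 + 0.84)² / 0.25 ≈ 63. That, and the word medium, make d = 0.5 a relevant case. Eight points equals d = 0.5 only if the SD is 16.

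**Formulas** (n per arm, noncentral F):

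- ANCOVA at one follow-up: λ = (n/2)d²/(1 − ρ²), df 1 and 2n − 3.
- ANCOVA on the mean of both follow-ups: replace 1 − ρ² by (1 + ρ)/2 − ρ².
- Group-by-phase interaction: λ = (n/2)Σc²/(1 − ρ), df 2 and 2(2n − 2), where c are the group differences at the three phases after centring. A sustained effect (0, d, d) gives Σc² = 2d²/3; a gradual one (0, d/2, d) gives d²/2.
- Group main effect, sustained: mean difference 2d/3, variance factor (1 + 2ρ)/3, df 1 and 2n − 2.

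**Worked case**, n = 80, d = 0.5, ρ = 0.5:

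- ANCOVA: 40 × 0.25/0.75 = 13.3, power 95.2%.
- Interaction, sustained: 40 × 0.1667/0.5 = 13.3, power 91.3%. The noncentrality is the same, but it is spread over two degrees of freedom.
- Main effect: 40 × 0.1111/0.6667 = 6.7, power 72.8%.

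**Power (%) with 80 completers per arm, d = 0.5**

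| ρ | ANCOVA, one follow-up | ANCOVA, mean of two follow-ups (sustained) | Interaction, sustained | Interaction, gradual | Main effect, sustained |
|---|---|---|---|---|---|
| 0.3 | 90.9 | 98.7 | 79.1 | 66.0 | 81.8 |
| 0.5 | 95.2 | 99.4 | 91.3 | 81.2 | 72.8 |
| 0.7 | 99.3 | 99.9 | 99.2 | 96.2 | 64.9 |

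**Smaller effect**, d = 0.4 sustained, interaction against single-visit ANCOVA: 59% v 75% at ρ = 0.3, 74% v 83% at 0.5, 93% v 94% at 0.7, and 98.9% v 98.7% at 0.8. The gap closes as ρ rises.

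**The article's effect size**, 80 per arm, ρ 0.3 to 0.7. At d = 0.80 ANCOVA is about 100%, the interaction 97.5-100% and the main effect 96.3-99.6%. At d = 1.26 all are about 100%.

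**The case against.** The strongest reply is that a group-by-phase mixed ANOVA is a valid and widely used test of differential change in a randomised trial, and that the sentence speaks of analysing changes, which points to the interaction. That is fair. The main-effect column above shows only what happens if that term were chosen; nothing in the article says it will be.

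A reader might go further than the text allows in four ways.

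- **That the trial is underpowered.** Not shown. At 0.4 as f or f², power stays above 90% under either method after 20% loss, and the article says that loss was allowed for. The shortfall appears only at smaller effects, and its size depends on a correlation the article does not give.
- **That the mixed ANOVA is imposed on every outcome and cannot be run for some.** The sentence is limited to measures taken at all three time points. The diary review and the event outcomes fall outside it, so no wrong model is assigned to them. Their between-arm method is not in this article and may stand in a fuller plan.
- **That incomplete patients will be dropped.** This is a property of the classical procedure. The article states no complete-case rule.
- **That naming partial η² prevents a judgement against eight points.** It has neither direction nor unit, but naming it does not exclude reporting mean differences and intervals.

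What survives is the conflict between the two sections, the use of a pre-randomisation value as an outcome level, and the unnamed test term. None of these depends on ρ or d.

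**Conclusion.** The point stands as an inconsistency in the primary analysis, with a nearly free gain in efficiency from resolving it. The planned model treats baseline as an outcome and gives no effect at a stated time. It is generally less efficient than a baseline-adjusted analysis: at d = 0.5 sustained with 80 completers per arm, 79-99% power for the interaction against 91-99% for ANCOVA at one follow-up and about 99% or more for ANCOVA on both. The loss is larger if the effect builds gradually (66-96% for the interaction). For a sustained effect against single-visit ANCOVA it is negligible at ρ of about 0.7 and above.

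These ranges rest on compound symmetry, an assumed ρ of 0.3 to 0.7, and an effect smaller than the article's printed one. The article's power statement is therefore not contradicted. The effect of the classical method on who is analysed is a risk to be closed off, not a stated rule.

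**What to change.** Make the analysis section match the Sample size section:

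- **SCHFI scores and other continuous measures with a baseline.** Use ANCOVA at each follow-up, or a linear mixed model of the two follow-ups with the baseline value as covariate plus group, assessment and group × assessment. Include all randomised patients with any follow-up, and name the contrast and time point that test treatment.
- **Reporting.** Give the adjusted mean difference with 95% CI and set it against eight points. Partial η² can remain as a supplement.
- **SCHFI management.** State how patients without recent symptoms at a visit are handled. The baseline-adjusted model no longer needs a score at all three visits, but dependence on symptoms at baseline and at the follow-up concerned remains.
- **Diary and self-care review.** Compare the arms at follow-up, adjusting for baseline SCHFI.
- **Readmission and survival.** Use count or time-to-event models from randomisation.

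The cost is revised wording and slightly more analysis work. No new data are needed. The trial status says that recruitment is continuing, so the change can be settled before outcome data are examined.

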I.*Patient clinical and socio-demographics*: age, gender, education level, social support, employment history. Patient clinical history, blood pathology (B-type natriuretic peptide (BNP), urea, electrolytes, full blood count), echocardiographic assessment of left ventricular systolic and diastolic function and assessment of valvular function, HF aetiology and treatments (medications, devices, surgery), physical examination (heart rate, blood pressure, respiratory rate, weight).II.*Heart Failure Screening Tool* (Heart-FaST) [36]: assesses three functional domains salient to patient engagement in self-care: physical, cognitive and emotional functioning. Higher scores on each barrier scale indicate worse functioning. Preliminary analyses support the construct validity of the Heart-FaST as a screening tool for physical, cognitive and emotional barriers that may hinder engagement in HF self-care. Heart-FaST, therefore, has the potential to assist clinicians in tailoring educational and surveillance disease management strategies to individual need [37].III.*Self-Care Heart-Failure Index* (SCHFI) [38]: assesses HF self-care behaviours and skills comprising 15 items rated on a 4-point scale to measure the process of self-care. There are three sub-scales: maintenance, management and confidence. Responses from each of the 3 self-care scales are transformed to a 100 point scale; higher scores reflect superior self-care. Self-care management scores are only computed for those patients reporting HF symptoms of ankle swelling or trouble breathing in the previous three months. Scaled scores > 70 are considered adequate self-care [38].IV.*European Heart Failure Self-care Behaviour Scale* (*EHFScBS*) [39,40]: 4 items from this scale will assess consulting behaviours in response to increased dyspnoea, feet swelling, weight gain and fatigue. Scores on the consulting subscale range from 4 to 20 with higher values indicating a lower likelihood of contacting providers for guidance when a change in signs or symptoms suggests worsening HF.V.*The Control Attitudes Scale - Revised* (CAS-R) [41]: assesses cardiac patients’ subjective perceived control in relation to managing their heart condition. Each of the 8 items is measured on a 5-point Likert scale ranging from 1 (strongly disagree) to 5 (strongly agree). Internal consistency in the HF population was Cronbach’s α = 0.76, and it showed good construct validity [41]. This scale will be administered to the HF patients, and will be adapted for administration to the caregivers. For example, one item on the CAS-R states: ‘If I do all the right things, I can successfully manage my heart condition’, and will be adapted for caregivers to state: ‘If I do all the right things, I can successfully manage the patient’s heart condition’. Similar amendments have been made in other studies investigating the perceived control of caregivers of patients with cardiac disorders [42,43].VI.*Short-Form 12-item health survey* (SF-12) [44]: assesses quality of life. The health survey consists of 12 items on a Likert response: 1) physical functioning, 2) physical role, 3) bodily pain, 4) general health, 5) vitality, 6) social functioning, 7) emotional role, and 8) mental health. Summary scale scores can be transformed to a scale of 0 to 10, with higher scores representing better health [44].VII.*The ‘Up and Go’ test* [45]: assesses functional mobility; stand from sitting, walk at usual speed for 3 meters, turn and return to sitting. To allow for test effect, an average of two timed trials will be recorded. The test is a measure of balance, walking ability and risk of falling in older populations and has been shown to be consistently reliable in test-retest analysis in patients with chronic conditions, including HF [45].VIII.*Dyadic HF care typology* [46,47]: describes the caregiving relationship between the HF patient and nominated carer. Both the HF participant and their carer will, independently, identify how their relationship functions in terms of managing HF symptoms. Care relationship types have been operationalised into: 1) caregiver responsible for the majority of the care of the HF patient, 2) HF patient responsible for the majority of their own care, 3) caregiver and the HF patient equally responsible for all aspects of the care, or 4) caregiver and the HF patient responsible for different aspects of the care.IX.*Hospital Anxiety and Depression Scale* (HADS) [48]: assesses anxiety and depression. Seven of the 14 items relate to anxiety and 7 relate to depression. Responses are provided on a Likert scale, and scores on each scale are interpreted in ranges: normal (0 to 7), mild (8 to 10), moderate (11 to 14), and severe (15 to 21). The 2 subscales have a mean correlation of 0.56, the mean Cronbach’s α is 0.83 for anxiety and 0.82 for depression [49].X.*Montreal Cognitive Assessment* (MoCA) [50]: screens for mild cognitive impairment in the domains of: visual-spatial skills; executive functions; language; attention; concentration; working memory; memory recall; and orientation. Low educational attainment is corrected by adding 1 point to the participant’s final score for ≤ 12 years of formal education. The highest possible score is 30 and a score 26 and above indicates normal cognitive function [50].

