### Outcomes

Primary study outcomes are patient engagement in HF self-care behaviours from both self-report (SCHFI) and the objective assessments from the carer, researcher and nurse, described above. Secondary outcomes are those not directly related to HF self-care behaviors but relevant to HF: quality of life; BNP, ‘Up and Go’ test, hospital readmissions, survival and transfer effects. To examine near to far transfer effects of the cognitive training we shall use PM tests aligned (or similar) to the training task, MIST and Virtual Week for near transfer effect. To examine for far transfer effects we will reassess overall cognitive function at Assessments One and Two. The TIADL and naturalistic PM task will assess transfer to everyday functioning, and will potentially represent somewhere between near and far transfer.

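### The plan sets clinical importance at eight points on the self-care score, but the only effect measure it fixes is partial eta-squared, which has no sign or units and cannot itself be read against eight points

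*Protocol article*

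**What the plan says.** All references are to the protocol article.

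- **Threshold.** Sample size, citing an outside source, says that "an eight-point difference in standardised self-care scores is a clinically important change".
- **Scale.** The SCHFI entry in the list of patient measures says: "Responses from each of the 3 self-care scales are transformed to a 100 point scale; higher scores reflect superior self-care". A group effect on these scores therefore has a direction and a unit.
- **Primary outcome.** Under Outcomes: "Primary study outcomes are patient engagement in HF self-care behaviours from both self-report (SCHFI) and the objective assessments", the latter coming from carer, researcher and nurse.
- **Comparison assumed for power.** Sample size: "Using analysis of covariance (ANCOVA) to examine for clinically significant differences in standardised self-care maintenance and management scores" between the two HF groups.
- **Analysis planned.** Statistical analyses: "we will use separate mixed ANOVAs for all dependent variables", with testing phase (baseline, Assessment One, Assessment Two) as the within-patient factor and training group as the between-patient factor.
- **Effect measure.** The same section closes by setting α at 0.05 for all analyses and, for all of them, saying that "effects sizes will refer to partial η-square values".

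Study design places Assessment One 2 to 4 weeks, and Assessment Two 12 months, after training.

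**The concern.** The threshold and the effect measure are in different currencies. Eight points is a signed quantity on a 100-point scale. Partial eta-squared is the share of variance attributed to a model term after the other terms are removed. It cannot be negative, carries no unit, and for a term with 2 degrees of freedom it collapses two contrasts into one number.

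The term that tests whether change over time differs by arm is the phase-by-group interaction. With three phases and two groups it has (3 − 1)(2 − 1) = 2 degrees of freedom. With follow-ups shortly after training and at 12 months, two questions matter: how many points the arms differ by, and whether the difference lasts. The specified measure answers neither by itself. If no estimate in points is named in advance, any reading of the result against eight points is left to be chosen once the data are seen.

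**Working it through.** **The plan's own figures.** The article states more than 90% power for 100 per group at f² = 0.4 and α = 0.05. A noncentral F with 1 numerator df, one covariate and λ = f²N = 0.4 × 200 = 80 gives power of about 1.00, so the statement is met. The 63 per group at 80% power is reproduced by a two-mean comparison at a standardised difference of 0.5. Neither figure is tied to eight points, because no SD is given. With f² = 0.4, d = 2√0.4 = 1.26, and eight points equals that only if the SD is 8/1.265 = 6.3.

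**Inputs for the check.** From the article: 100 patients per arm, three phases, two groups, eight points. Assumed, because the article gives neither: SD 15 to 25, and equal correlation ρ between visits of 0.3 to 0.7. No loss to follow-up is modelled.

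**Formulas for the interaction.** Let d_t be the arm difference at visit t and d̄ its mean over the three visits.
- S = Σ((d_t − d̄)/2)²
- SS_interaction = 2 × 100 × S
- SS_error = 2 × 198 × SD²(1 − ρ)
- Partial η² = SS_interaction/(SS_interaction + SS_error)

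**Step 1: different outcomes, same S.** Profiles are differences at baseline, Assessment One and Assessment Two.

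| Profile | d̄ | Σ(d_t − d̄)² | S |
|---|---|---|---|
| Lasting benefit (0, +8, +8) | 5.33 | 28.44 + 7.11 + 7.11 = 42.67 | 10.67 |
| Fully faded benefit (0, +8, 0) | 2.67 | 7.11 + 28.44 + 7.11 = 42.67 | 10.67 |
| Harm (0, −8, −8) | −5.33 | 28.44 + 7.11 + 7.11 = 42.67 | 10.67 |
| Half-faded benefit (0, +8, +4) | 4 | 16 + 16 + 0 = 32 | 8.00 |

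The error term does not involve the profile, so the first three rows share F, p and partial η² whatever the SD and correlation.

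**Step 2: values at SD 20, ρ = 0.5.** SS_error = 396 × 400 × 0.5 = 79,200.
- First three profiles: SS_interaction = 200 × 10.67 = 2,133; partial η² = 2,133/81,333 = 0.0262; F = (2,133/2)/(79,200/396) = 5.33; p = 0.005.
- Half-faded profile: SS_interaction = 200 × 8 = 1,600; partial η² = 1,600/80,800 = 0.0198.

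**Step 3: the same eight-point effect under other assumptions.**

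| SD | ρ = 0.3 | ρ = 0.5 | ρ = 0.7 |
|---|---|---|---|
| 15 | 0.033 | 0.046 | 0.074 |
| 20 | 0.019 | 0.026 | 0.043 |
| 25 | 0.012 | 0.017 | 0.028 |

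**Step 4: reading backwards.** Let D be the size in points of a lasting difference (0, D, D). Then S = D²/6, so D = √[(0.06/0.94) × SS_error/33.33] for a partial η² of 0.06. This gives 7.2 points at SD 15, ρ = 0.7 (SS_error = 26,730) and 18.2 points at SD 25, ρ = 0.3 (SS_error = 173,250).

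**Step 5: the group main effect.** At SD 20, ρ = 0.5 its partial η² is 0.0262 for lasting benefit, 0.0067 for fully faded benefit and 0.0262 for harm. It separates lasting from faded benefit, but not benefit from harm.

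**The case against.** Naming partial eta-squared as the effect-size index does not mean that group means will be withheld. A mixed ANOVA rests on the six group-by-phase means, and these show direction and points. This stands: a reader might infer that the trial could not tell whether eight points was reached or reversed, and the article does not support that. What it lacks is a named estimate and interval for that judgement.

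A second objection is that visit-specific contrasts and confidence intervals are details a journal article leaves to a full protocol or analysis plan. Their absence alone would be no finding. The article, however, makes a positive choice of effect measure for all analyses, and that choice does not fit the threshold stated one section before.

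Third, a reader might infer that partial eta-squared is always the same for lasting benefit, fading benefit and harm. It is not. The equality of lasting and faded benefit holds only for the interaction and only when the benefit vanishes completely. A half-faded benefit gives a different value, and the group main effect separates the two. Only the symmetry between benefit and harm is general, and it is common to all such F tests.

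Fourth, the power statement for 200 patients uses f², which is also a variance-explained measure, so the effect-size metric does match the power metric. That is correct. A reader might infer that the trial was sized on eight points, but without an SD the article does not establish this. Agreement with the power metric still leaves the clinical threshold without a matching estimate.

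**Conclusion.** The mismatch is real and lies within the article: clinical importance is stated in points, and the only effect measure fixed is unsigned and unit-free. The interaction's equal value for benefit and harm of the same size, and for lasting and fully faded benefit, is algebraic and needs no assumption about SD or correlation. The translation between points and partial eta-squared does need them. Over the assumed ranges, eight points maps to a roughly sixfold spread of values (0.074/0.012 ≈ 6), so the index cannot stand in for the threshold.

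The consequence is limited. The data would be unharmed and the means would still be available. What is missing is a pre-stated estimate with an interval that answers the question the plan poses in points, at each of its two follow-ups. The point is worth correcting and does not depend on the power calculation.

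**What to change.** In Statistical analyses, replace the effect-size clause with wording such as:

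> For the SCHFI maintenance and management scores, the effect measure is the baseline-adjusted difference in means between arms (PM training minus word puzzles), in scale points with 95% CI, at Assessment One and at Assessment Two. Each interval will be read against the eight-point threshold given under Sample size. Partial η² will be reported as a supplement.

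The estimate should come from ANCOVA, which Sample size already names, or from an equivalent baseline-adjusted repeated-measures model. A reader might expect the planned mixed ANOVA to supply it unchanged, but that model treats baseline as a level of the within-patient factor and so yields differences in change from baseline. Because the article computes the management score only for patients with recent symptoms, the sentence should also say which patients that estimate covers.

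The cost is a small change of model and one or two sentences. No new data or visits are needed, and the two sections would then agree on the method of comparison.
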